**Fig 1 pone.0292864.g001:**
[figure not shown]
Timeline. Clinical, neurophysiological, postural and cognitive assessment timeline for adolescents girls with AIS assisted with corrective postural exercises (AIS 1), adolescent girls with AIS treated with both corrective postural exercises and partial or full-time brace (AIS 2) and CTRL. Tables report for each group and for each phase (T0, T1, T2) which parameters will be recorded. The personal and clinical parameters and experimental protocol block descriptions are reported in the lower panel (1), (2), (3), (4), (5), (6), (7).

#### Materials and equipment

Motion capture data will be acquired from our 10-camera stereophotogrammetric system at 100 Hz. The motion capture system includes a control box (Lock Synch Box, Vicon) to synchronously record analog force plate data (Bertec 4060–10, Bertec Corporation, Columbus, Ohio, United States), IMU and sEMG data (WaveTrack IMU and MiniWave, Cometa srl, Milan, Italy), which will be sampled at 2000 Hz. The sEMG signals will be filtered between 20–450 Hz. EEG data will be acquired from 64 channels at a sampling frequency of 500 Hz and will be referenced to Cpz (ANT Neuro, Enschede, The Netherlands). The synchronization between the stereophotogrammetric system and the portable EEG system will be guaranteed by a custom-made MATLAB script, which instructs and uses a trigger box (BrainTrends, Rome, Italy) to send: (i) the start acquisition command to the Vicon system (responsible for stereophotogrammetric, EMG, IMU and force platforms data collection); and (ii) a time stamp to the EEG system, which is already recording.

### Procedure

All methods will be carried out in accordance with the guidelines of the 2008 Helsinki Declaration. Ethical approval has been obtained on April 2023. Written informed consent will be provided by both subjects and their legal guardians.

We estimate recruiting 40 subjects. Considering a 20% dropout (approximately 8 subjects), we expect to acquire data from 30 subjects (15 subjects with AIS and 15 CTRL). For the calculation, we used the average effect size observed in [3] (i.e., the minimum difference between CTRL and AIS subjects for the EEG laterality index in sensorimotor areas) considering error probability (*α*) of 5%, with a power (1 –*β* error probability) of 80%. Power statistical analyses will be repeated after having recorded data at T0 as an additional tool to review the required sample size. If necessary, the sample size will be enlarged.

#### Selection criteria

Control subjects—Inclusion criteria:

sample size: N ≥ 15 subjectssex: femaleage range: 11–16 yearsright-handednessnormal body mass index (BMI) (between 18.5 and 24.9 kg/m^2^)

Control subjects—Exclusion criteria:

spinal pathology or any known neurological or musculoskeletal disordersclinically relevant back humppresence of any trunk alterationintake of any drug with a central nervous disease effectdermatologic problemssporting activity at competitive level (≥ 10 h/week) or involving balance-enhancing activities

AIS subjects—Inclusion criteria:

sample size: N ≥ 15 subjectssex: femaleage range: 11–16 yearsright-handednesswith mild (Cobb angle ranging from 10° to 20°, no spine surgery) and moderate (21–35°, no spine surgery) scoliosisnormal BMI (between 18.5 and 24.9 kg/m^2^)

AIS subjects—Exclusion criteria:

severe scoliosis (Cobb angle > 35°, possible spine surgery required)already treated with brace or corrective postural exercisesintake of any drug with a central nervous disease effectdermatologic problemssporting activity at competitive level (≥ 10 h/week) or involving balance-enhancing activities

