## Introduction

Adolescent idiopathic scoliosis (AIS) is the most common form of scoliosis, affecting approximately 1–3% of adolescents (10–18 years of age) [1]. AIS is a three-dimensional morphological spinal deformity that typically manifests a translation and rotation of the spine in the frontal and horizontal planes, and most of the time a reduction in the physiological curves of the rachis in the sagittal plane. AIS significantly changes the structure and appearance of the adolescent spine, thorax, and trunk [2, 3]. The severity of scoliosis is typically assessed through the Cobb angle, which is the angle between the endplates of the upper and lower end vertebrae—the vertebrae with the largest angle to the horizontal—measured from X-rays. This parameter is considered the standard method to quantify the severity of scoliosis as well as to evaluate the need for treatment, monitor the progression of the curve, and estimate the success of therapy [4]. The Scoliosis Research Society suggests that diagnosis is confirmed when the Cobb angle is greater than 10° or the axial rotation is identified [2] using the Perdriolle method [5] or the Nash and Moe method [6].

Treatment options include conservative management (bracing) or operative intervention [2]. In approximately 20% of cases, scoliosis is secondary to another pathological process, while the remaining 80% are cases of AIS [2]. Several studies on the onset and progression of AIS report a higher prevalence and severity of the curve in girls [1–3, 7]. Research is needed to identify gender-specific risk factors [7]. The cause and pathophysiology of AIS appear complex and remain unclear. To date, the causes of scoliosis have mainly been sought in congenital or acquired disorders of the vertebral structure [2]. The causes of scoliosis are supposed to be systemic disorders of, among others, mucopolysaccharide and lipoprotein synthesis [2]. On the one hand, a dysfunction of postural mechanisms involving the central nervous system (CNS) and a distorted body schema have been proposed to be part of a sequence of pathological events in the development of spinal deformity in AIS [8, 9]. On the other hand, CNS alterations have also been explored as a possible cause of AIS [3, 10–15].

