Taking into account the results of the state-of-art literature, the primary objective of this experimental protocol is to quantitatively investigate alterations of body representation in AIS. We believe that a quantitative evaluation of body representation alterations in AIS in a longitudinal study may provide new information to better understand the pathophysiology and etiology of scoliosis. The novelty of our study is also based on including the evaluation of girls with AIS before any treatment. We cannot exclude a priori that altered brain activations of the sensorimotor network, altered body schema and image, increased attention toward shoulders and back could be a consequence of treatment per se. Physical therapy exercises and brace treatment could increase proprioception and awareness of the shoulder and back muscles. Our longitudinal study aims to rule out the hypothesis described above.

Results from our previous study, conducted on subjects with AIS who underwent brace treatment, [3] revealed: (i) a significant increase in relative power of EEG delta ([1–4] Hz) and theta rhythms, compared to controls, located in central areas; a significant increase in the laterality index in alpha range observed in adolescents with AIS with main right curve, demonstrating an imbalance between the two sensorimotor areas; (ii) no differences in balance performances between groups; (iii) no differences between controls and adolescents with AIS for the single body segment. However, the investigation of body schema revealed possible alterations in the overall representation of the trunk, namely in the perception of the shoulders-waist proportion, and in its inclination. Based on the literature background and our previous work [3], we expect that, compared to controls, adolescents with AIS, before any treatment, will show: (i) altered brain activation of the sensorimotor network; (ii) greater sway, unbalanced activation of muscles on the right and left sides of the back, and more variable IMU signals on the frontal plane when performing the target reaching, as a result of less efficient control of their balance on the plane with the larger scoliotic deformity; (iii) altered body schema reflecting altered activation of the sensorimotor network.

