## Materials and methods

### Experimental design

Adolescent girls with a confirmed diagnosis of mild (Cobb angle ranging from 10° to 20°, no spine surgery) and moderate (Cobb angle ranging from 21° to 35°, no spine surgery) scoliosis (AIS) will be enrolled at the Adolescence Spine Diseases Diagnostic and Therapeutic Center of the Padova University Hospital. Subjects matched in sex and age without AIS—controls (CTRL)—will be recruited through flyers posted in middle and high schools in Padova.

Adolescent girls with AIS and controls will undergo a three-phase experimental protocol (T0, T1, T2).

This longitudinal study aims to follow and quantify alteration in body representation in parallel to the progression of scoliosis from the time of the first diagnosis by the physiatrist (T0) and up to one year after diagnosis (T1, T2). At T0, subjects (AIS and CTRL) will undergo two tasks aimed at investigating possible alterations in *body schema* representation. During the experiment, we will use EEG to record changes in brain oscillations; sEMG to assess possible imbalances in muscle activation, IMUs, motion capture, and force platforms to monitor the performance and movement characteristics during the balance and motor tasks. A self-reported questionnaire and a computer-based test will be administered to all subjects to investigate *body image* alterations in AIS.

After this evaluation (T0), if the adolescent shows low-grade scoliosis, an expert physiotherapist gives her corrective postural exercises to perform daily (30 min / day) until growth is complete. Participants’ performance in scoliosis-specific exercise will be monitored by the physiotherapist at least once a week. The set of exercises is believed to improve postural awareness, proprioception, and ability to dissociate the movements of the lumbar spine from the thoracic one in the different planes of space. Treatment will be planned in the individual patient, based on the dysfunction detected in the clinical assessment. When scoliosis exceeds the 20°Cobb and there is evidence of progression risk, a rigid partial (18 hours/day) or full-time brace (23 hours/day) is also prescribed.

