#### Clinical assessment

Before undergoing the experimental protocol, the following data will be recorded for each subject: age, weight, height, BMI, sexual maturity, evaluated according to information related to menarche, and physical activity. Handedness will be evaluated using the Oldfield Questionnaire [28].

During their first medical examination, adolescents with AIS will undergo a physical assessment performed by a physiatrist to (i) detect the presence of possible body asymmetries and (ii) measure the paravertebral humps in the forward bent position with the Bunnell scoliometer and the Ferraro humpmeter [29, 30]. All subjects will be evaluated by the same physiatrist to ensure data repeatability and minimize intersubject measurement error. A standing full-spine posterior-anterior x-ray will be performed. The curve entity will be quantified using the Cobb angle method [31], while the Perdriolle method will be applied to estimate the rotation of the apical vertebrae [5]. Based on the radiological image, the physiatrist will also collect other relevant clinical measures, i.e., the initial correction rate (ICR), the side and anatomical site of the convexity of the scoliosis, trunk asymmetries, shoulders, and hips inclination. Radiological examination will be repeated only at T2 to avoid excessive radiation exposure in adolescent girls, allowing clinicians to quantify possible variations in the values of the parameters. The progression of AIS will be defined as a worsening of more than 5°Cobb in the magnitude of the curve during the duration of the study (approximately one year). Therapy specifics (e.g., brace type, prescription, compliance, duration of exercise) will be reported both for subjects who will be treated with a partial or full-time brace and for those who will only be assisted with corrective postural exercises (for more details, see Fig 1).

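### Known neurological and musculoskeletal disorders exclude controls but not girls with AIS, so a T0 group difference cannot be attributed cleanly to scoliosis

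*Protocol article*

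**What the plan says.** The Selection criteria section of the protocol article prints separate lists for the two groups. The control exclusions include "spinal pathology or any known neurological or musculoskeletal" disorders, besides a relevant back hump and any trunk alteration. The AIS exclusions open with "severe scoliosis (Cobb angle > 35°, possible spine surgery" and continue with earlier brace or exercise treatment, CNS-acting drugs, skin problems and competitive or balance-training sport. The last three items appear in both lists. No AIS item concerns neurological disease or a musculoskeletal disorder other than the curve itself.

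Under Experimental design, the groups are comparable by matching on two variables only: "Subjects matched in sex and age without AIS". The Introduction predicts that untreated girls with AIS will show, against controls, "altered brain activation of the sensorimotor network", more sway and muscle imbalance during reaching, and an altered body schema.

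**The concern.** Some differences between the two lists are unavoidable. A control must be free of spinal pathology, hump and trunk alteration, because that is what makes her a control. The neurological and musculoskeletal item is different: it is a general-health filter, and it is applied to one side only.

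The outcomes are EEG rhythms, centre-of-pressure sway, muscle activation and reaching accuracy, all of which an unrelated neurological or limb disorder can alter. If such girls can enter the AIS group but not the control group, a T0 difference has two possible sources, scoliosis and coexisting disease. The Discussion and Conclusion want to use that difference for biomarkers and for the pathogenic mechanism. The Procedure section also plans to repeat the power calculation on the T0 data, so a distorted contrast would carry over into the sample size review.

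**Working it through.** **Does other text close the gap?**

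- *Idiopathic diagnosis.* The Introduction states: "In approximately 20% of cases, scoliosis is secondary to another pathological process, while the remaining 80% are cases of AIS". This removes girls whose curve is caused by another disease. It does not remove a condition unrelated to the curve.
- *CNS-drug exclusion, both groups.* This removes some treated neurological disease, but not an unmedicated condition or a limb disorder.
- *Clinical assessment.* The text says "adolescents with AIS will undergo a physical assessment performed by a physiatrist", and describes asymmetries, humps and X-ray measures. It names no neurological screen as an entry condition. Experimental design mentions neurological evaluations, but as study assessments that are repeated, not as an eligibility rule.
- *Data for later adjustment.* The listed variables are age, weight, height, BMI, maturity, physical activity and handedness. Comorbidity is not among them, although Fig 1 is not shown and may list more.

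What remains eligible in AIS but not in controls is an unrelated, unmedicated neurological condition or a musculoskeletal disorder outside the spine.

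**The plan's own figures.** Procedure gives 40 recruited, 20% dropout, 15 + 15 evaluable, α 5% and power 80%. The dropout step is close: 40 × 0.8 = 32 against 30, and 30 / 0.8 = 37.5, so 38 against 40. The 15 per group cannot be reproduced, because no effect size is stated. Solved backwards, 15 per group with a two-sided two-sample t-test implies a detectable difference of 1.06 SD. The normal approximation gives (1.960 + 0.842) × √(2/15) = 1.02 SD.

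**Size of the distortion (assumed inputs).** Let k of 15 AIS girls have such a condition and let it shift the outcome by c SD. The documents give neither k nor c.

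- Shift of the AIS mean = (k/15) × c. For c = 2: k = 1 gives 0.13 SD and k = 2 gives 0.27 SD.
- Relative to 1.06 SD: 0.133/1.06 = 13% and 0.267/1.06 = 25%.
- Expected AIS sample variance = 1 + c² × k(15 − k)/(15 × 14). For c = 2: k = 1 gives 1.267 (SD 1.13) and k = 2 gives 1.495 (SD 1.22). The affected girls widen the error term as well as moving the mean.

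Rejection rate of a two-sided 5% two-sample t-test, 15 against 15, no scoliosis effect, all affected girls shifted the same way, 40,000 simulated trials per row:

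| Affected girls (k) | Shift c (SD) | Shift of mean (SD) | Rejection rate |
|---|---|---|---|
| 1 | 1 | 0.07 | 5.1% |
| 2 | 1 | 0.13 | 5.7% |
| 1 | 2 | 0.13 | 4.8% |
| 2 | 2 | 0.27 | 7.4% |
| 3 | 1 | 0.20 | 7.3% |
| 3 | 2 | 0.40 | 11.2% |

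If the direction of the shift is random, one or two girls at 2 SD leave the rate at about 5%.

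**The case against.** The case against has real weight. Entry requires a confirmed diagnosis at a specialist spine centre and an examination by a physiatrist, and the drug, sport and handedness criteria are common to both groups. It would be wrong to infer that girls with AIS enter with no health filter at all. This stands, and it narrows the gap to unrelated conditions.

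A reader might also infer that the asymmetry necessarily pushes the contrast towards a difference. The documents do not support that. The measure used for sizing, the EEG laterality index, is a signed right-versus-left contrast, and nothing says that an unrelated condition would move it to one side. Without a common direction the condition adds variance and does not shift the mean. Expressing the shift as 13% to 25% of the detectable difference also sounds larger than its effect on the test, because the same girls inflate the error variance.

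The longitudinal aim is largely spared, since a stable condition mostly cancels in each girl's change from T0.

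A further tempting reading is that the fixed "body mass index (BMI) (between 18.5 and 24.9" kg/m² band, used from age 11 to 16, biases the comparison as well. It does not: the band is the same in both groups and the groups are age-matched. Whether it selects against younger girls depends on BMI-for-age figures that the documents do not give.

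Finally, this is a condensed article. That carries little weight here, because both lists are printed item by item and differ.

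**Conclusion.** The point holds as a one-sided eligibility criterion that leaves a possible confounder in the T0 AIS-control comparison of EEG, sway and reaching. The asymmetry is certain from the text. Its effect is probably modest: with 1 to 2 of 15 girls shifted 2 SD in one direction, the mean moves 0.13 to 0.27 SD and false positives run at about 5% to 7%. Reaching 11% takes 3 of 15 girls at 2 SD. These figures rest on assumed frequency, size and common direction, and on an independent two-sample t-test. The point does not extend to within-girl change or to the BMI band. It is worth correcting because the T0 contrast carries the mechanistic conclusion and the correction is cheap.

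**What to change.** Add one line to the AIS exclusions: *any known neurological disorder, or musculoskeletal disorder other than AIS*. If enrolment is already complete (Project timeline gives a June 2023 start and recruitment in months 1–5), record such conditions in both groups instead, and report the AIS-control comparison with and without the affected girls.

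The cost is a short amendment and possibly a few excluded girls with AIS. The planned numbers do not change. If the line is added partway through recruitment, girls enrolled earlier came in under the old rule, so the with/without comparison should be reported in that case too.

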#### Clinical assessment

Before undergoing the experimental protocol, the following data will be recorded for each subject: age, weight, height, BMI, sexual maturity, evaluated according to information related to menarche, and physical activity. Handedness will be evaluated using the Oldfield Questionnaire [28].

During their first medical examination, adolescents with AIS will undergo a physical assessment performed by a physiatrist to (i) detect the presence of possible body asymmetries and (ii) measure the paravertebral humps in the forward bent position with the Bunnell scoliometer and the Ferraro humpmeter [29, 30]. All subjects will be evaluated by the same physiatrist to ensure data repeatability and minimize intersubject measurement error. A standing full-spine posterior-anterior x-ray will be performed. The curve entity will be quantified using the Cobb angle method [31], while the Perdriolle method will be applied to estimate the rotation of the apical vertebrae [5]. Based on the radiological image, the physiatrist will also collect other relevant clinical measures, i.e., the initial correction rate (ICR), the side and anatomical site of the convexity of the scoliosis, trunk asymmetries, shoulders, and hips inclination. Radiological examination will be repeated only at T2 to avoid excessive radiation exposure in adolescent girls, allowing clinicians to quantify possible variations in the values of the parameters. The progression of AIS will be defined as a worsening of more than 5°Cobb in the magnitude of the curve during the duration of the study (approximately one year). Therapy specifics (e.g., brace type, prescription, compliance, duration of exercise) will be reported both for subjects who will be treated with a partial or full-time brace and for those who will only be assisted with corrective postural exercises (for more details, see Fig 1).

#### Experimental protocol

Subjects will be asked to wear a top stretch and a pair of shorts. Before starting the recordings, snap-lead sEMG sensors will be placed bilaterally on the belly of the muscle of the erector spinae, latissimus dorsi, and abdominal muscles (rectus abdominis, abdominal external oblique, abdominal internal oblique) as indicated in S1 Appendix. Sensors will be placed along the direction of the muscle fiber after shaving the skin to remove excess hair, and cleaning the skin with an alcohol swab to remove sweat and dirt. The quality of the sEMG signal will be ensured by visually inspecting the signals for low baseline noise at rest and the absence of low-frequency motion artifact during movement [32]. Wearable IMU devices (accelerometer, magnetometer, and gyroscope) will be placed with a double-sided adhesive tape on the fifth lumbar vertebra (L5) and bilaterally on the tibia. The impedance values of the EEG sensors will be recorded, checked, and stored at the beginning and end of the experiment. The whole protocol will last approximately 80 min and will be repeated once at each experimental phase. The protocol consists of five blocks. First, subjects will undergo (i) a resting state recording as a baseline and (ii) Maximal Voluntary contractions. Second, the body schema will be investigated through tasks based on the (iii) target reaching, and (iv) forearm bisection task. Blocks (iii)-(iv) will be administered in random order. Eventually, the perception of body image by subjects will be investigated through (v) a cognitive and behavioral evaluation (Fig 1). We refer the reader to S1 Appendix for a detailed description of the implementation of tasks.

*(i) Resting-state recording (6 min)*. will be performed before executing the two tasks as a baseline condition. A 6-min EEG resting state recording of quiet upright standing (without shoes) will be acquired in a sound-attenuated room, first with eyes open, looking at a fixation cross (∼ 3 m in front of the subjects), and then with eyes closed. Participants will be instructed to keep their feet position parallel and at shoulder width. COP sway will be recorded using a force platform. Acceleration and angular velocity data gathered from the IMU placed on the lower back will be processed to estimate pelvis motion during the standing trial and quantify participants’ balance control performance [33, 34]. Pelvis kinematics will also be evaluated through the motion capture system. This will allow checking whether the use of a waist-mounted IMU produces reliable quantities to assess AIS subjects stability in clinical settings, without demanding for a motion capture laboratory.

*(ii) Maximal Voluntary Contractions (MVCs) (10 min)*. will be performed to estimate the maximum sEMG amplitude for signal normalization. Subjects will be asked to perform isometric contractions against resistance as detailed in S1 Appendix to maximally activate each muscle tested. 5 min of rest between trials will be provided to avoid fatigue accumulation. We will also ask the subject if she may need longer rest time. Subjects will be carefully instructed, trained, and encouraged to ensure maximum exertion. (The placement of electrodes on the muscle and the procedures for acquiring a voluntary movement contraction (MVC) of each muscle are detailed in S1 Appendix).

*(iii) Target reaching (15 min)*. The task will assess the influence of body schema on the planning of the movement. Subjects will start with their hand on their chest and observe the experimenter, standing next to them, touching (for 3 s) one of the 10 targets (represented in Fig 2A) displayed with different shapes and color and placed at different x-y position on the board. Then, they will be instructed to reach the same point before returning to the starting position with the hand at the chest, keeping their eyes closed. The 10 targets will be presented to the subjects in a randomized order. The same task will be repeated both with the dominant and with the non-dominant hand. The Euclidean distance between the x-y coordinates of the two points (experimenter- and subject-selected) will be calculated for each target as a measure of the precision of task execution (see S1 Appendix for further details).

